### Efficacy evaluation outcomes

Participants will complete the following measures at (1) baseline, (2) immediately after introduction to the intervention, and (3) at one-month follow-up.Likelihood of offering/referring or taking up CBT will be measured using a single Likert scale (0–10) for how likely the participant is, in general, to offer/refer psychosis patients for CBT, if this were available, or how likely the participant is to take up CBTp if it were offered today, each rated from not at all (0) to extremely likely (10);Knowledge and attitudes towards CBTp will be measured using mean factor score for two new questionnaires developed during earlier phases of the current study. The clinician questionnaire comprises 27 items, which form three factors (pro CBT content, supportive CBT culture, confidence in the value of CBT to patients), all with high internal consistency (α = 0.87, 0.82 and 0.71, respectively) and predictive validity for likelihood of referring/offering CBTp (robust estimate of correlation = 0.45, 0.53 and 0.32, respectively). The patient questionnaire comprises 35 items, which form four factors (positive attitudes towards CBTp, personal barriers, doubt regarding efficacy and fear related to CBTp), each with good internal consistency (α = 0.94, 0.83, 0.76 and 0.82, respectively) and predictive validity (robust estimate of correlation = 0.50, 0.46 and 0.54, respectively), except fear which was not a good predictor of uptake (robust estimate of correlation = 0.26). In each questionnaire, items are scored on a 7-point Likert scale from disagree strongly to agree strongly;Illness perceptions will be measured using the mean factor scores for the modified illness perceptions questionnaire [55] which has good internal consistency (α = 0.70) and forms three factors (cure/control, timeline, causes). The cure/control and timeline factors have good internal reliability and test–retest reliability (cure/control α = 0.09/0.09 and timeline α = 0.7/0.06). Individual items are scored on a 5-point Likert scale from strongly agree to strongly disagree;Attitudes and behaviours towards CBTp implementation will be measured using mean scores for five constructs of the NOMAD tool [56] adapted for CBTp implementation (clinicians only). The tool includes three items that assess normalisation of CBTp on a 0–10 Likert scale from ‘still feels very new’ to ‘feels completely familiar’, and 20 items that assess the four core constructs of coherence of CBTp with standard care, cognitive participation, collective action and reflexive monitoring, each rated on a 5-point Likert scale from strongly agree to strongly disagree;Psychological wellbeing will be measured using the CHOICE short-form measure of psychological wellbeing (patients only). This scale has been produced by our research group and has good psychometric properties including internal consistency (α = 0.83), test–retest reliability (ICC = 0.73), convergent validity (*r* = 0.52 with quality of life; − 0.58 with mood) and sensitivity to change (*t* = − 0.41) [57]. The short form used in the current study has been widely used including in the national IAPT-SMI pilot sites in the UK [30], and includes 11 items, and one personal goal item, each rated on a 0–10 Likert scale from ‘worst’ to ‘best’. The total mean score will be used;Empowerment will be measured using the mean factor scores for the Rogers’ Empowerment scale (patients only) [58] which has good internal consistency (α = 0.82) and factor structure with five factors: self-esteem (α = 0.82); perceived power (α = 0.59); optimism and control over the future (α = 0.45); community activism/autonomy (α = 0.59); and righteous anger (α = 0.64), with good convergent (hope/recovery *r* = 0.67, empowerment *r* = 0.45) and predictive validity (psychosis symptoms *r* = − 0.39). The scale includes 28 items measured on a 4-point Likert scale from strongly agree to strongly disagree;CBT-related activities in the preceding month will be based on interview and case notes screen (at one-month follow-up).

The interview regarding CBT-related activities is part of a larger interview to explore attitudes to and use of the intervention during the follow-up period. The whole interview takes approximately 10 min.

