**Methods:**

The design is a two-arm, feasibility randomised controlled trial (RCT), with 1:1 randomisation, stratified by participant group and site. Participants are 40 psychosis patients and 40 clinicians, who are ambivalent towards uptake or implementation of CBTp. Sites are community and inpatient services in Sussex and London. The intervention is a pre-CBT digital psychoeducation intervention designed to address identified knowledge and attitudinal barriers to uptake and implementation of CBTp, incorporating behaviour change mechanisms, and supported by animated introductory, patient and clinician stories. The comparator is the NHS choices website for CBT. The primary aim is to assess clinical feasibility (recruitment, randomisation, acceptability, use, delivery, outcome measurement, retention). A secondary aim is a preliminary evaluation of efficacy. Outcomes will be assessed at baseline, post intervention, and one-month follow-up (blind to treatment arm). The primary efficacy outcome is likelihood of offering/taking up CBTp. Secondary outcomes include knowledge and attitudes towards CBTp, illness perceptions, empowerment, psychological wellbeing (patients only) and CBTp implementation (clinicians only). Use of the intervention and CBT behaviours during the follow-up period will be recorded and captured in a feedback questionnaire. Use, acceptability and experience of outcome assessment will be explored in qualitative interviews with participants (*n* = 6 per group). The efficacy evaluation will report descriptive data, key model parameters and 95% highest probability density intervals in a Bayesian growth model.

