### Aims and objectives

This is the first feasibility RCT to develop and test a pre-CBT digital ‘informed choice’ psychoeducation intervention, designed to address identified knowledge and attitudinal barriers to uptake by psychosis patients and offers by clinicians of CBTp, and ultimately to improve implementation. The primary research aim is to explore trial methods, clinician and patient acceptability of the interventions and outcome measures, and to provide data to estimate the parameters required to design a future RCT. The primary objectives are as follows:To determine the number of participants who accept referral and randomisation (benchmark set at 80% of target for progression);To evaluate the appropriateness of eligibility criteria (ambivalence towards CBTp) by determining feasible eligibility and recruitment rates at each site;To assess retention through post-intervention and one-month follow-up rates (benchmark set at minimum 80% retention in line with previous studies);To assess acceptability of the intervention, and factors influencing this, through usage data in the follow-up period, feedback questionnaire responses, and qualitative interviews;To assess the acceptability and feasibility of the outcome measures as methods to measure efficacy of the intervention within a future trial.

Secondary objectives will be:To measure and describe key outcomes post intervention and at one-month-follow up (e.g. completion rates, likelihood of offering/referring or taking CBT). Descriptive statistics will be used to quantify dropout and differences in mean responses on key outcome measures over time within each arm. Contingent upon the similarity of protocol for a future trial to this feasibility trial, Bayesian models may be fit to determine plausible estimates for the effect of the trial under both informative and uninformative priors.

We will not report significance tests as the feasibility RCT was not designed or powered to test hypotheses or to detect change. We have selected the NHS choices information about CBT as the comparison intervention as this is the next best alternative online resource about CBT that is routinely available for use by NHS clinicians and the public.

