The intervention will be delivered during a manualised introductory session of up to 1-h duration, by a trained research assistant. Access to the intervention will be available for the subsequent month by computer or iPad, before follow-up. No specific instructions will be given for how or when participants should access the intervention, but overall usage data will be recorded. Images of the intervention are shown in Fig. 3.

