### Primary feasibility outcomes

The primary purpose is to assess the feasibility of the interventions in terms of acceptability, usability and accessibility, and to examine the feasibility of methods of a future trial including measures, recruitment procedures and trial processes. This will be done through monitoring using the study CONSORT diagram, through system analytics on use of the digital intervention during the one-month period, through the user feedback questionnaire collected at the end of one month, and through a qualitative interview with a sub-sample of those receiving the intervention (*n* = 6 per group) at the end of one month. The primary feasibility outcomes are:Feasibility of eligibility criteria, recruitment and retention within the NHS (numbers referred, recruited, consented, randomised and retained in the trial) during the trial recruitment period of August 2017 to May 2018;Feasibility of use, accessibility and acceptability of the intervention and the outcome measures in the NHS, measured using feedback questionnaire responses regarding use of the intervention; activity data on use of the intervention during the follow-up period (average number of pages visited per participant), qualitative interviews with six patients and six clinicians (three each in Sussex and London) regarding their experience of using the intervention, the selection of outcome measures and participation in the trial; September 2017 to May 2018.

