## Procedure

Clinician and patient participants will be identified through research staff presentations at team meetings, clinics, training events and following email and telephone contact with staff.

Clinician participants will be approached by a research assistant and patient participants by their lead clinician. All interested potential participants will be provided with the study information sheet and will have the opportunity to discuss the study in a meeting or telephone conversation with a research assistant who is trained in taking informed consent and in Good Clinical Practice. Following informed consent, participants will complete the basic demographic information and baseline questionnaire measures. They will then be randomised to either the intervention or comparison condition. The intervention or comparison condition will be provided according to a manualised protocol as part of a single session lasting up to 1 h, after which participants will also complete the same questionnaires in the post-intervention assessment in the same session.

Participants in the intervention condition will be provided with access to the online intervention for the subsequent month. Where a patient participant does not have access to a computer, they will be provided with an iPad, locked to the intervention site, to enable access in the subsequent month. Usage data will be tracked through Google Analytics and will be stored safely and confidentially; data willonly be accessible to the researchers via a password. Usage data will be stored in an encoded format that prevents tampering. Comparison participants will be provided with the NHS choices website link and handout. This website is publicly available. After one month (− 2/+ 8 weeks), each participant will complete the same questionnaires in a follow-up assessment, which will be conducted by a research assistant who is blind to randomisation arm, in person or by telephone. All participants in the intervention arm will also complete a brief feedback questionnaire on their use of the intervention.

A small subsample of six patients and six clinicians who receive the informed choice intervention materials will also undertake a brief semi-structured interview with a research assistant to explore their experience of using the intervention materials and to provide feedback to further refine the intervention.

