### Trial status

Recruitment of participants commenced in August 2017 and will be open until May 2018. The date of first enrolment is August 2017.

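### CBT activity is counted over the month before a visit that may fall anywhere from about week 2 to week 12, so the count covers different periods in different participants; retention also has no stated end date beyond recruitment

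*Protocol article*

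**What the plan says.** Four statements in the protocol article bear on the CBT-activity outcome and its timing.

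- Efficacy evaluation outcomes fixes the look-back: "CBT-related activities in the preceding month will be based on interview and case notes screen (at one-month follow-up").
- Procedure fixes when that visit may happen: "After one month (− 2/+ 8 weeks), each participant will complete the same questionnaires in a follow-up assessment".
- Intervention describes the exposure period: "Access to the intervention will be available for the subsequent month by computer or iPad, before follow-up".
- The Methods paragraph of the abstract gives a different observation period: "Use of the intervention and CBT behaviours during the follow-up period will be recorded and captured in a feedback questionnaire".

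Three further statements bear on retention.

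- Aims and objectives sets the benchmark: "To assess retention through post-intervention and one-month follow-up rates (benchmark set at minimum 80% retention in line with previous studies").
- Primary feasibility outcomes dates the counts of participants "randomised and retained in the trial) during the trial recruitment period of August 2017 to May 2018". It dates the use and acceptability outcomes from September 2017 to May 2018.
- Trial status says: "Recruitment of participants commenced in August 2017 and will be open until May 2018".

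**The concern.** CBT-related activity is the listed outcome that records what participants did about CBT, as distinct from what they know, believe or intend. Its look-back is tied to the visit date, and the visit date can move by ten weeks. Followed as written, an early visit counts activity from before randomisation as an outcome. A late visit leaves out the period in which participants had been given access to the website. Counts from different participants then describe different stretches of time, and the abstract's definition would give different counts again. A future trial that used these data to choose or size a behavioural outcome would inherit that mixture.

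The retention issue is smaller. Retention at the follow-up visit is placed inside the recruitment period, and recruitment is open until the month in which that period ends. The text does not say how participants who join near the end are to be counted. Retention is one of two numerical benchmarks in the objectives, so its numerator and denominator need to be unambiguous.

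**Working it through.** **Visit window.** Input: one month, minus 2 and plus 8 weeks (Procedure). With a month of 4 weeks, 4 − 2 = 2 and 4 + 8 = 12, so the visit falls at weeks 2 to 12. With a calendar month of 4.35 weeks the range is 2.35 to 12.35, which changes nothing of substance.

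**Look-back.** Take the session as week 0. Randomisation follows baseline immediately and precedes delivery, so it is also week 0. Let m = 4 weeks be both the look-back and the access month, and t the week of the visit. Then:

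- weeks of look-back before randomisation = max(0, m − t)
- weeks of look-back inside the access month = max(0, min(m, t) − max(0, t − m))
- share of the interval from session to visit that is covered = min(t, m) / t

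| Visit (week) | Look-back covers weeks | Before randomisation | Inside access month | Share of follow-up covered |
|---|---|---|---|---|
| 2 | −2 to 2 | 2 of 4 (50%) | 2 weeks | 100% |
| 4 | 0 to 4 | 0 | 4 weeks | 100% |
| 8 | 4 to 8 | 0 | 0 weeks | 4/8 = 50% |
| 12 | 8 to 12 | 0 | 0 weeks | 4/12 = 33% |

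The preceding month and the follow-up period coincide only at week 4. From week 8 onward the look-back contains none of the access month.

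**Retention dates.** The protocol gives months, not days, so I assume even accrual of 80 participants from 1 August 2017 and a count that closes on 31 May 2018. To fit before that date, randomisation must occur by 17 May for the opening of the window (2 weeks), by 3 May for the nominal visit (4 weeks), and by 8 March for the full window (12 weeks).

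*Recruitment to 31 May (304 days):*

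- cannot reach the opening of the window: 14/304 = 4.6%, or 3.7 of 80
- cannot reach the nominal visit: 28/304 = 9.2%, or 7.4 of 80
- window cut short or not reached: 84/304 = 27.6%, or 22.1 of 80

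*Recruitment to 1 May (274 days):*

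- cannot reach the opening or the nominal visit: 0
- late end of the window cut short: 54/274 = 19.7%, or 15.8 of 80

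**Effect on the benchmark.** The benchmark is 0.80 × 80 = 64 participants. Suppose recruitment runs to 31 May and those who cannot reach the opening are counted as lost. True retention of 85% then reads as 0.85 × (1 − 14/304) = 81.1%, a drop of 3.9 points that still passes. Under the same assumptions, true retention below 0.80 / (1 − 14/304) = 83.9% would read as under 80%. With recruitment stopping by 1 May, every participant can be seen at the nominal visit and no loss is forced.

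**The case against.** On CBT activity, the strongest reply is that weeks 2 and 12 are the extremes of the window. The match is exact at the nominal visit, and no distribution of visit times is given, so the typical error is unknown. The outcome is secondary and descriptive, carries no benchmark, and is collected under the same window in both arms by a blinded assessor. The case-notes screen could recover dates outside the look-back. All of this stands, and I claim no bias between arms. It does not reconcile the two definitions, and the protocol permits visits over the whole range.

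On retention, a reader might infer that the calendar alone would make the trial miss its benchmark, since 85% would read as 0.85 × (1 − 28/304) = 77.2%. That requires recruitment and data collection both to run to 31 May, even accrual, participants not yet due to be counted as lost, and nobody to be seen before the nominal date. The protocol states none of these, and the last conflicts with its own window. The wording on recruitment can equally mean a stop as May begins. Procedure says each participant will complete the follow-up, and the May 2018 date is attached to the feasibility outcomes, not to all data collection.

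A reader might also object that someone first reached at week 12 should not count as retained at one month. The wide window is prespecified, and a feasibility trial may use one to learn what follow-up is achievable. The protocol offers no basis for a narrower cut-off.

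**Conclusion.** The CBT-activity point holds. The look-back and the visit window fit together only near week 4, and the abstract states a different period. The size runs from no mismatch at week 4 to half the look-back before randomisation at week 2, and to no overlap with the access month from week 8 onward. How much this affects the trial's summary depends on the spread of visit dates, which the protocol does not give.

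The retention point holds only as a lack of clarity. The count is tied to a recruitment period with no follow-up time stated after it. The effect on reported retention ranges from none, if recruitment stops by about 1 May, to about 4 percentage points at a true rate of 85%, if recruitment and data collection both end on 31 May and accrual is even. That upper figure counts only participants who could not reach the opening of the window. Losses from windows cut short cannot be sized without visit times. The 80% benchmark is a chosen progression criterion and is not in error.

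**What to change.** **CBT activity.** Start the count at the intervention session. Either use a fixed interval, such as the first month after it, with dated entries from the interview and the case notes, or report activities per week from the session to the actual visit. Use the same definition in the abstract and in the outcome list. The cost is a small change to the form and somewhat longer recall for participants seen late, which the case-notes screen partly offsets.

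**Retention.** State a follow-up end date separate from the close of recruitment, set when the last participant's window closes. That is about 12 weeks after the last randomisation: about 24 July 2018 if recruitment stops on 1 May, or about 23 August 2018 if it runs to 31 May. Use all randomised participants as the denominator, and report the timing of follow-up visits descriptively beside the retention rate. The cost is a sentence or two of wording and a later close of the feasibility data, or an earlier close of recruitment.

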## Method

### Design

The design is a two-arm, multicentre, longitudinal, feasibility RCT, with 1:1 block randomisation and varying block size, stratified by participant group (clinician or patient) and site (London or Sussex). Participants will be randomised by Kings College London Clinical Trials Unit, independently from the trial team, using an online randomisation system. Randomisation will be initiated by the research assistant immediately after the baseline assessment and before intervention delivery. Allocation will be confirmed by email. Baseline and one-month follow-up data will be collected blind to allocation to ensure unbiased data collection. Post-intervention data will not be collected blind to allocation as these data are collected in a single session, immediately after intervention delivery. Participants will not be blind and will be reminded of the blind procedure at the start of the one-month follow-up, in order to reduce the risk that they reveal their allocation, and blind breaks will be recorded. For reporting the feasibility of the RCT, the CONSORT (Consolidated Standards of Reporting Trials; http://www.consort-statement.org/) extension to randomised pilot and feasibility trials statement will be followed [54]. For the protocol, the SPIRIT (Standard Protocol Items: Recommendations for Interventional Trials) Figure and Checklist are provided in this paper see: Fig. 1 and Additional file 1.

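### Blinding of the one-month CBT-activity interview is not secured, because its questions sit inside an interview about using the intervention

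*Protocol article*

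**What the plan says.** **Blinding.** The Design section says: "Baseline and one-month follow-up data will be collected blind to allocation to ensure unbiased data collection". It names one exception, the post-intervention assessment, which takes place in the same session as delivery. The Methods paragraph of the abstract also describes the one-month assessment as blind. The Procedure section says of the follow-up assessment, in which participants repeat the questionnaires: "which will be conducted by a research assistant who is blind to randomisation arm, in person or by telephone". Participants know their arm. The safeguards in the Design section are a reminder of the blind procedure at the start of the visit and a record of blind breaks.

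**The outcome.** CBT-related activity is on the list under Efficacy evaluation outcomes. It is measured at one month from an interview and a screen of the case notes. The paragraph after the list adds: "The interview regarding CBT-related activities is part of a larger interview to explore attitudes to and use of the intervention during the follow-up period". Its full length is given as about 10 minutes.

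**The feedback form.** The Procedure section says: "All participants in the intervention arm will also complete a brief feedback questionnaire on their use of the intervention". Primary feasibility outcomes places its collection at the end of the month. The abstract says: "Use of the intervention and CBT behaviours during the follow-up period will be recorded and captured in a feedback questionnaire".

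**The concern.** An interviewer who asks how a participant has used the intervention is likely to learn which arm that participant is in. A form given to one arm only identifies the arm to whoever hands it over. If either comes before the CBT-activity answers are recorded, those answers are not taken blind, although the Design section says they are.

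Two things are at stake. CBT-related activity records what participants did during the month, as distinct from how likely they say they are to take up or offer CBT. The blind-break record should tell the designers of the next trial whether a blind follow-up is workable. If the visit itself prompts disclosure, the record will mix those breaks with the ones a better-arranged visit would still have.

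**Working it through.** No arithmetic applies: the article gives no figure for blinding, for the frequency of CBT activity or for any bias. The check is a comparison of the statements.

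1. **Does the blinding claim cover this outcome?** Yes. The Design sentence covers all one-month data and exempts only the post-intervention assessment. CBT-related activity is an efficacy evaluation outcome measured at one month.

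2. **Does the larger interview reveal the arm?** There are two readings.
   - If it is put to the intervention arm only, being interviewed identifies the arm.
   - If it is put to both arms, the question alone need not identify the arm. The Comparator section also calls the NHS website an intervention, and comparison participants receive its link. But a participant who describes the site they used gives the arm away.

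3. **Who conducts the interview?** The article does not say. There are again two cases.
   - If the blind assistant conducts it, the CBT-activity answers are blind only if they are recorded before any question on use. No such order is stated, and the CBT-activity questions are described as part of the use interview.
   - If an unblinded colleague conducts it, the interview-based part of the outcome is not collected blind, contrary to the Design section.

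   The general claim therefore either fails for this outcome or depends on an order the article does not give.

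4. **What does the feedback form add?** With 1:1 randomisation of 40 patients and 40 clinicians, about 80 / 2 = 40 participants would be due the form at full retention. The abstract puts use and CBT behaviours in a feedback questionnaire, and the Procedure section gives the questionnaire on use to one arm. Read together, these suggest that part of the CBT-behaviour information may be recorded on a form that only one arm receives. The sections should be reconciled.

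5. **Do the safeguards reach this?** The reminder asks participants to withhold what the use questions then invite them to say. The log would capture such breaks, since the article does not restrict it to accidental ones, but it cannot prevent them.

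6. **How far does the effect spread?** The Analysis plan reports CBT-related behaviour descriptively. The parameter it singles out in the Bayesian growth model concerns likelihood of taking up or referring to CBT, which participants who know their arm rate themselves. Questionnaires completed before any talk of use are not touched. Order matters more when follow-up is by telephone, if items are then read aloud; that is an assumption, as the article does not describe how they are administered.

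**The case against.** The strongest reply is that the article never says the blind assistant runs the use interview or handles the feedback form. The Procedure section ties that assistant to the questionnaires, and the form appears in a separate sentence with no administrator named. Visit order and staffing are commonly left to the full protocol, and the SPIRIT figure to which the article refers is not shown. The case-notes screen can be done blind. The NOMAD measure also covers clinicians' behaviour, so this is not the trial's only record of behaviour. No significance tests are planned, and the review after 10 participants per group offers a route for correcting procedures.

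Most of this stands, and it limits the point. A reader might infer that the assessor is necessarily unblinded by the visit, that the blinding is therefore fictitious, or that the arm of all 80 participants becomes known by elimination. The documents support none of these, because each needs the blind assistant to meet the form or the use questions before recording outcomes. Nor can a reader put a size on the bias: the article gives neither an expected frequency of CBT activity nor a coding rule.

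The objection does not remove the conflict. That conflict lies between sentences that are present: an unqualified claim of blind collection, and an outcome interview described as part of an interview on use. Naming a different interviewer would not rescue the claim if that person were unblinded.

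**Conclusion.** The point holds in a limited form. As written, blinding of the interview-based part of the CBT-activity outcome is not secured, and it conflicts with the statements in the abstract and the Design section that one-month data are collected blind.

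The consequence is confined to one descriptively reported outcome and to the usefulness of the blind-break log. This rests on the self-rated questionnaires being completed before any discussion of use, which the article does not state. No numerical bias is claimed. The matter still merits correction because exploring trial methods is part of the primary aim, and the follow-up procedure is meant to inform a future trial.

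**What to change.** - Take the CBT-activity questions out of the interview on attitudes and use.
- Fix the order of the one-month visit. The blind assessor completes all questionnaires, then asks CBT-activity questions that mention neither website, and locks the record.
- Place every question on use, the feedback form and any iPad return after that lock, or give them to the assistant who delivered the session.
- Have the case notes screened by someone blind to arm.
- Bring the abstract's account of the feedback questionnaire into line with the Procedure section, so that CBT behaviours are recorded in the same way in both arms.

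If the team prefers to keep the interview as it is, amend the abstract and the Design section to say that the CBT-activity outcome is not assessed blind.

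The cost is protocol wording, a visit checklist and an occasional hand-over between assistants. No extra visit or staff are needed.
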